Newer approaches to clinical research offer an opportunity to generate high-quality evidence for guiding patient management, including in complex and rare diseases. These innovations, including nesting of studies within registries or large cohorts, pragmatism and healthcare embedding, and outcome or response-adaptation, focus on informing real world decision-making, may be more conducive to high levels of participation, and may offer greater flexibility and statistical efficiency than traditional clinical trials [9, 10]. Such approaches enable multiple treatment questions to be addressed concurrently or sequentially, according to research priorities and prespecified protocol adaptation rules [9].

Here, we present a core protocol for studying the management of PEx in the BEAT CF (Bayesian Evidence Adaptive Treatment for people with Cystic Fibrosis) platform. The PEx core protocol sets out the establishment of a prospective, multi-site cohort designed to perpetually enroll and follow-up people with CF and systematically capture data on the management and outcomes of any PEx requiring intensive therapy (PERIT). Here, a PERIT is pragmatically defined as an acute or subacute deterioration in lung function or symptoms resulting in (possibly multimodal) therapy comprising initiation of at least one intravenous antibiotic. It is anticipated that most cohort participants will become eligible to participate in cohort-nested sub-studies, including a PEx Treatment Platform in which selected aspects of PERIT management will be randomly assigned.

The protocol documentation for BEAT CF is modular and hierarchical (Fig. 1) to facilitate nesting of the PEx Treatment Platform and other cohort-nested sub-studies, to minimize redundancy in the documentation, and to maximize consistency and standardization across the cohort and any nested projects. Here, we describe the core objectives, endpoints, data collection, and study procedures for the PEx cohort, along with plans for the analysis and reporting of their data. All current approved versions of the BEAT CF protocol documentation are available at https://www.beatcf.org.au/beat-cf/.

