For each PERIT, we will also report the following outcomes measured as the following endpoints:The change in lung function up to 6 months after commencement of intensive therapy, *measured as* the absolute change in the ppFEV_1_ from initiation of intensive therapy until approximately 14 days (≥ 14 days to < 30 days), 30 days (≥ 30 days to < 60 days), 60 days (≥ 60 days to < 90 days), and 180 days (≥ 180 days to < 240 days) after commencement of intensive therapyThe change in lung function up to 6 months after commencement of intensive therapy, *measured as: (i)* the proportional change (expressed as a percentage) in the ppFEV_1_ from initiation of intensive therapy until 7 days (≥ 7 to < 10 days), 14 days (≥ 14 days to < 30 days), 30 days (≥ 30 days to < 60 days), 60 days (≥ 60 days to < 90 days), and 180 days (≥ 180 days to < 240 days) after commencement of intensive therapy; (ii) the return of measured lung function to close to its baseline (pre-exacerbation) best function, up to 6 months after commencement of intensive therapy, *measured as* a binary outcome of whether the ppFEV_1_ has returned to ≥ 90% of the ppFEV_1_ at baseline, at approximately 7 days (≥ 7 to < 10 days), 14 days (≥ 14 days to < 30 days), 30 days (≥ 30 days to < 60 days), 60 days (≥ 60 days to < 90 days), and 180 days (≥ 180 days to < 240 days) after commencement of intensive therapy, where the baseline ppFEV_1_ is the highest recorded ppFEV1 in the 180 days (or 365 days if no ppFEV_1_ < 180 days) preceding the commencement of intensive therapyThe change in CF-related symptoms up to 4 weeks after commencement of intensive therapy, *measured as* the absolute change in the Chronic Respiratory Infection Symptom Score (CRISS) score approximately 7 days (≥ 7 to < 10 days), 14 days (≥ 14 days to < 30 days), 30 days (≥ 30 days to < 60 days), after commencement of intensive therapyThe time to the next PERIT, *measured as* the time (in days) from commencement of intensive therapy to the next commencement of intensive therapy, after a period of no intensive therapy of ≥ 7 daysAdverse reactions resulting in treatment cessation, *measured as* any early termination of planned therapy before 7 days (7*24 hours) and before 14 days (14*24 hours) after commencement of intensive therapy, owing to one or more adverse events presumed by the responsible clinician to be attributable to the prescribed therapyTreatment failure resulting in treatment cessation, *measured as* any early termination of planned therapy before 7 days (7*24 hours) and before 14 days (14*24 hours) after commencement of intensive therapy, owing to inadequate improvement in symptoms or lung function, presumed by the responsible clinician to be attributable to a poor response to the prescribed therapy

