The decision was made for the primary outcome to be absolute rather than relative change in the ppFEV_1_ for two reasons. Firstly, mean absolute change in FEV_1_ has been shown to have lower variability than relative change [18]. Secondly, relative changes in FEV1 are non-symmetric for increasing versus decreasing changes. For example, if half of participants experience a change in ppFEV_1_ from 50 to 100 (+100% increase), and the other half experience a change from 100 to 50 (− 50% change) the net change in ppFEV_1_ will be + 25% (i.e., (− 50% + 100%)/2 = 25%), rather than zero.

Importantly, additional endpoints will be captured which include safety, effects on microbiology, and more patient-centered outcomes such as the CRISS (symptom score) which provides information that is complementary to lung function measurements and which captures different aspects of clinical response [18].

There is no consensus regarding the optimal endpoints for children with CF who are too young to perform spirometry [13]. Lung clearance index (LCI) [19] and structural lung disease captured by radiological imaging have been proposed as alternative outcome measures in this age group [20]. LCI in children < 6 years old has been shown to correlate with abnormal lung function and structural lung disease at school age entry [21]. Computerized tomography (CT) scores have been found to correlate with clinical status, lung function and disease progression and are predictive of mortality [22]. However, use of LCI and radiological imaging such as CT or magnetic resonance imaging (MRI) are currently restricted to the research context, because these investigations are not routinely performed, and interpretation of their results lacks standardization [22]. While these outcome measures are not included as part of the proposed data capture for BEAT CF, they may be considered for inclusion in the future.

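### The secondary endpoint of return to at least 90% of baseline ppFEV1 has no condition on the starting value, so PERITs that begin above the line count as returned without any change

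*Protocol article*

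**What the plan says.** Background and rationale {6a} defines a PERIT as "an acute or subacute deterioration in lung function or symptoms resulting in (possibly multimodal) therapy comprising initiation of at least one intravenous antibiotic". Deterioration in lung function and deterioration in symptoms are alternatives, so no fall in FEV1 is required.

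Outcomes {12} introduces its list of further endpoints with "For each PERIT, we will also report the following outcomes measured as the following endpoints". One of them, listed under change in lung function, is "a binary outcome of whether the ppFEV_1_ has returned to" at least 90% of its baseline value, scored in five windows from about 7 to about 180 days. Its reference is fixed in the same sentence: "the baseline ppFEV_1_ is the highest recorded ppFEV1 in the 180 days" before intensive therapy starts, or 365 days if there is no value within 180. Nothing there limits the endpoint to PERITs whose initiation value is below the 90% line, or treats those above it separately.

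On analysis, adjustment for baseline differences is written into the primary effect measure in Outcomes {12}. For endpoints in general, Statistical methods {20a} permits chi-squared and Fisher's exact tests, and plans Bayesian regression for predictors of treatment outcomes, including binary ones. Intervention description {11a} leaves treatment to the treating team outside nested sub-studies.

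**The concern.** The endpoint is worded as a return, which implies that function was lost first. For a PERIT that begins within 10% of the prior best, nothing has to be regained: the criterion is already satisfied when therapy starts, and the episode succeeds at every later time point by staying where it is.

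Two consequences follow. First, episodes that start above the line and remain there contribute the same success in both groups and no information on recovery, so the observed difference is smaller than the difference among episodes with something to recover. Randomisation in a nested trial does not remove this. Second, in the observational cohort the share starting above the line may differ between treatments because clinicians choose them. A treatment used more often for symptom-only episodes would then show a higher return rate with no better recovery.

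**Working it through.** The documents give no figure for the share affected and no recovery rate, so there is no plan figure to reproduce for this endpoint. The rule can be checked exactly; the sizes below rest on stated assumptions.

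**1. The rule applied to single cases** (threshold from Outcomes {12}). With baseline 80 the line is 0.9 × 80 = 72. Initiation values of 80, 76 and 72 (100%, 95% and 90% of baseline) already meet it; 71.9 (89.9%) does not. Any PERIT with a relative drop of 10% or less satisfies the criterion before treatment. The endpoint is first assessed at 7 days, so this means the criterion is satisfied at Day 0, not that it is scored then.

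**2. Share already at or above the line.** Assume a normally distributed relative drop from baseline at initiation, with mean m and SD s (neither is in the documents). Share f = Φ((10 − m)/s).

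| Mean drop m | SD 8 | SD 12 |
|---|---|---|
| 10% | Φ(0) = 0.50 | Φ(0) = 0.50 |
| 15% | Φ(−0.625) = 0.27 | Φ(−0.417) = 0.34 |
| 20% | Φ(−1.25) = 0.11 | Φ(−0.833) = 0.20 |

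**3. Dilution.** Assume that PERITs starting above the line stay there in both groups, and that return among the rest is 50% versus 65%. Each observed rate is f + (1 − f)p, so the observed difference is (1 − f) × 15 points. The n per arm is for 80% power at two-sided 5%. The last column is 170/(1 − f), rounded up: the PERITs per arm that must be observed to leave 170 below the line.

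| f | Observed rates | Difference (points) | n per arm, all PERITs | PERITs per arm to yield 170 below the line |
|---|---|---|---|---|
| 0 | 50.0% v 65.0% | 15.0 | 170 | 170 |
| 0.1 | 55.0% v 68.5% | 13.5 | 203 | 189 |
| 0.2 | 60.0% v 72.0% | 12.0 | 244 | 213 |
| 0.3 | 65.0% v 75.5% | 10.5 | 297 | 243 |
| 0.5 | 75.0% v 82.5% | 7.5 | 466 | 340 |

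On these assumptions the restricted comparison is the more efficient one even after the excluded PERITs are paid for, although the gain is smaller than the fourth column alone suggests.

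**4. Case-mix.** Suppose 34% of one group and 20% of the other start above the line (the two SD 12 values for m = 15 and m = 20), and true return among the rest is 50% in both. Observed: 0.34 + 0.66 × 0.5 = 0.67 and 0.20 + 0.80 × 0.5 = 0.60. That is a 7-point difference with no difference in recovery. The imbalance is chosen for illustration.

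**5. Cost of restricting.** Selecting on one noisy reading invites regression to the mean. Simulation with no true change (assumed baseline 60, mean drop 15%, SD 10, independent noise on both readings): among PERITs reading below the line at initiation, 14% read at or above it later with noise SD 3, and 24% with noise SD 6.

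**The case against.** The strongest reply is that this is a status endpoint. It asks whether function is close to the prior best at 7 to 180 days, and that is worth knowing for every PERIT. An episode that starts at 92% and ends at 85% counts as a failure, which is informative, and a restricted analysis would discard it. This stands, and it is why the all-PERIT proportion should be kept.

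It is also fair that covariates and denominators are often settled in an analysis plan, which is not shown, and that Bayesian regression is foreseen for binary endpoints. But the protocol itself fixes the threshold, windows, reference value and unit of analysis; the gap is in that fixed definition.

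Restriction has its own bias, as step 5 shows. It inflates the absolute return rate, but applies equally to groups that are alike at initiation.

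The sizes are assumptions. Taking the highest value in 180 days as reference tends to lower the share starting above the line, and the 7-point example needs groups whose mean drops differ by 5 percentage points.

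A reader might also infer that the protocol contradicts itself by keeping "the proportional change (expressed as a percentage) in the ppFEV_1_ from initiation of intensive therapy" as a secondary endpoint when the Discussion says that "relative changes in FEV1 are non-symmetric for increasing versus decreasing changes". The documents do not support that. The Discussion uses the asymmetry only to explain why the primary outcome is absolute, and absolute change is reported at all the same time points (day 7 as primary, the rest as secondary). The endpoint is not defined as a mean, and Statistical methods {20a} provides medians for asymmetric distributions. The +25% in the Discussion comes from an illustration with 50-point swings and is not an estimate of bias. Under no true change the shift cancels between groups with the same distribution (simulated difference −0.01 points). A log ratio would be an optional preference.

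**Conclusion.** The point holds for the return endpoint. The definition lets a PERIT count as returned with no change, because the entry event does not require an FEV1 drop and the endpoint ignores the initiation value. That follows from the text alone.

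Its size does not. The affected share is unknown; about 11% to 50% is the range under assumed mean drops of 10% to 20% with SD 8 to 12. The shrinkage from 15 points to 12.0 (20% above the line) or 10.5 (30%) further assumes that those PERITs stay above the line in both groups. The case-mix effect could run in either direction in the cohort and needs an imbalance in starting status that the documents neither show nor exclude.

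This concerns one secondary endpoint and leaves the primary endpoint untouched. It should be corrected before comparative results on return are reported.

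**What to change.** In the definition of the return endpoint:

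- Report, by group and stratum, the share of PERITs with initiation ppFEV1 already at or above 90% of baseline.
- Make the comparative analysis of return the one among PERITs with initiation ppFEV1 below 90% of baseline; or keep all PERITs and adjust for, or stratify by, initiation ppFEV1 as a proportion of baseline.
- Keep the all-PERIT proportion at or above 90% as a descriptive measure of status, so that episodes which start above the line and then worsen remain visible.

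No new data are needed: FEV1 at Day 0 is in Table 2, and results from the 365 days before enrolment are in Table 1. The restricted version costs a smaller denominator and some regression to the mean in the absolute return rate, which should be stated when that rate is reported. The adjusted or stratified version keeps the denominator but needs a stated form for the covariate.

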#### Outcomes {12}

The primary estimand (inferential target for estimation) for each participant, for each PERIT, is defined by:*Study population:* People with CF with a PERIT who can perform spirometry and for whom there is reasonable equipoise about the most appropriate first line treatment regimen*Primary outcome and endpoint:* The change in lung function 7–10 days after commencing intensive therapy (therapy entailing use of at least one intravenous antibiotic), measured as the absolute change in percentage predicted forced expiratory volume in 1-s (ppFEV_1_) from initiation of intensive therapy (measured closest in time to the first dose on IV therapy, *and not* ≥ 14 days before, *and not* ≥ 72 hours afterwards) to the first measured ppFEV_1_ ≥ 7 days afterwards (measured closest in time to 7x24 hours afterwards *but not* ≥ 10 days (10x24 hours) afterwards)*Primary effect measure:* The absolute difference in the mean of the primary endpoint between those in the intervention versus the comparator group, adjusting for any differences in baseline factors between intervention and comparator arms that might otherwise confound or reduce the certainty of the treatment effect*Interventions:* Prescription of each intervention within a domain*Comparators*: Prescription of each other Intervention within that domain*Intercurrent events:* Participants will be included in the primary analysis irrespective of whether and how the intervention or comparator is received, any non-adherence, any subsequent change in therapy, or loss to follow-up, (i.e., the effect attributable to the prescription, or the treatment policy or de facto estimand)

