#### Participant timeline {13}

Once enrolled in the PEx Cohort, participants remain in the cohort until they withdraw, or until the project closes (see Criteria for Discontinuation above). The timing of individual PERITS varies between participants. Data collection occurs (1) at enrolment (cohort entry), (2) approximately every 3 months thereafter, and (3) with each PERIT (Fig. 3).

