	Date and details of any new, documented infection, or airway colonization	Y^a^	Y	The presence of specific pathogens may influence therapeutic choices, plausibly confounds or modifies treatment effects. Selection of resistant pathogens may be an untoward outcome of antibiotic therapy
	Date and details of any new, documented infection with *Clostridium difficile*	Y^a^	Y	*Clostridium difficile*-related diarrhea is an important untoward outcome of antibiotic therapy
**Patient-reported outcomes**:	Cystic Fibrosis Questionnaire-revised (CFQ-R) for all participants ≥6 years old	Y	Y	Treatment of PEx plausibly impacts on quality-of-life (QoL) over time
**Anthropometric**	Height	Y	Y	Height is associated with FEV_1_ and is essential for estimating the ppFEV_1_
	Weight	Y	Y	Treatment of PEx plausibly impacts on weight over time
**Spirometry**	FEV_1_	Y^b^	Y	Treatment of PEx plausibly impacts on lung function. The ppFEV_1_, is strongly associated with morbidity and mortality in CF

^a^Including results in the 24 months preceding enrolment into the cohort

^b^Including results in the 12 months (365 days) preceding enrolment into the cohort

**Table 2 Tab2:** Additional outcome data for each PERIT

	Variable	Timing	Reason
**PEx therapy**	Date and time of commencing IV therapy	Day 0	As a time reference point for analyses
**PEx therapy**	Location (hospital or HITH)	Daily	For description of the cohort. Location may constrain therapeutic options and plausibly confound or modify treatment effects
**Spirometry**	FEV_1_	Days 0 (at admission), 7, 14, 30, 60, and 180	Treatment of PEx plausibly impacts on lung function, measured as ppFEV_1_; this is strongly associated with morbidity and mortality in CF
**Clinical assessment**	Presence and quality of cough	Daily	Reduction in cough and/or improvement in cough quality are measures of successful treatment of PEx
	Presence of crepitations	Daily	Reduction in crepitations is a measure of successful treatment of PEx
**Patient-reported outcomes**	CRISS score (if > 12 years at admission)	Day 0: as close as practicable to the initiation of IV antibiotics, and not > 72 h afterwards, then days 7, 14, and 30	CRISS is a validated measure of CF-related symptoms in the preceding 24 h. It is expected that successful treatment will result in an improved CRISS score. It will be used to assess clinical response to treatment for PEx

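### The window for the pre-exacerbation best ppFEV1 does not exclude the exacerbation reading, so a lone pre-dose sick value blocks the 365-day fallback and return to baseline is overcalled in that subset

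*Protocol article*

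**What the plan says.** Outcomes {12} of the protocol article lists, among the further endpoints for each PERIT, "the return of measured lung function to close to its baseline (pre-exacerbation) best function". It is scored as "a binary outcome of whether the ppFEV_1_ has returned to ≥ 90% of the ppFEV_1_ at baseline", at about 7, 14, 30, 60 and 180 days. The baseline is the "highest recorded ppFEV1 in the 180 days (or 365 days if no ppFEV_1_ < 180 days) preceding the commencement of intensive" therapy. No days before the first IV dose are left out.

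The same section takes the start-of-therapy reading for the primary endpoint as the one "measured closest in time to the first dose on IV therapy, *and not* ≥ 14 days before, *and not* ≥ 72 hours afterwards". It may therefore fall on either side of the first dose. Table 2, under Plans for assessment and collection of outcomes {18a}, schedules PERIT spirometry at "Days 0 (at admission), 7, 14, 30, 60, and 180" and does not fix the order of the Day 0 reading and the first dose.

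Between PERITs, data are collected "approximately every 3 months thereafter" (Participant timeline {13}). Table 1 lists FEV1 at that frequency, and at entry it includes results from the preceding 12 months.

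**The concern.** A PERIT is a deterioration that leads to IV therapy, so the exacerbation has begun before the first dose. A window that ends at the dose can therefore contain readings from the exacerbation, although the endpoint is labelled pre-exacerbation.

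This matters most for the fallback. The 365-day extension serves people with no recent reading, yet any pre-dose sick reading counts as a recent one and closes it. The person is then compared with their own sick value. The same spirometry done after the first dose would lie outside the window, and the fallback would open. For these PERITs the order of spirometry and first dose, which the protocol leaves free, can decide the result. All five time points share the baseline, so the error carries through all of them.

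**Working it through.** The protocol gives no figure for this endpoint to reproduce. The check applies the written rule to worked cases and then asks how often the conditions could arise. The ppFEV1 values and missed-reading rates are assumptions.

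**1. The rule.** Baseline B = maximum ppFEV1 in the 180 days before the dose. If there is none, B = maximum in 365 days. Returned if follow-up / B ≥ 0.90.

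**2. Cases.** Stable value 80, sick value 60, Day 7 value 62.

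| Readings | B as written | Day 7 / B | Scored |
|---|---|---|---|
| Stable at day -200; sick before the dose | 60 (fallback blocked) | 62/60 = 103% | returned |
| Same, plus stable 80 at day -90 | 80 | 62/80 = 78% | not returned |
| Stable at day -200; sick after the dose | 80 (fallback opens) | 62/80 = 78% | not returned |
| Sick before the dose is the only reading in 365 days | 60 | 62/60 = 103% | returned, though no pre-exacerbation value exists |

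**3. Which follow-up values are misclassified.** In the first case the pass mark is 0.9 × 60 = 54 instead of 0.9 × 80 = 72. Any follow-up value from 54 to just under 72 is scored as returned when it falls short of 90% of the stable best. This includes an unchanged 60. In general the pass mark, as a share of the stable best, is 0.9 × (1 − relative drop): 81.0% for a 10% drop, 72.0% for 20%, 63.0% for 30%. Where the older stable value is higher than the sick one, the error can only favour returned.

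**4. How many PERITs could be affected.** Assume visits every 91.25 days at a random phase, each reading missed independently with probability m. Take days 14 to 180 before the dose as the span in which a stable reading would protect; 14 days is illustrative. That span is 166 days, and 166/91.25 = 1.819, so it holds two scheduled visits with probability 0.819 and one with probability 0.181. Hence

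P(no stable reading, days 14-180) = 0.181m + 0.819m².

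Simulation of the same model (200,000 draws per rate) also gives the share with a reading at days 180-365, where the fallback should have worked:

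| m | Formula | Simulated, none in days 14-180 | Of these, with a reading in days 180-365 (share of all PERITs) |
|---|---|---|---|
| 0 | 0% | 0% | 0% |
| 5% | 1.1% | 1.1% | 1.1% |
| 10% | 2.6% | 2.6% | 2.6% |
| 20% | 6.9% | 7.0% | 6.7% |
| 30% | 12.8% | 12.8% | 11.6% |

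Within this model the last column is an upper bound on wrong scores. The sick reading must also precede the dose, and the follow-up value must lie in the band of step 3. If missed visits cluster in the same people, the share could be higher than under independence.

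**The case against.** The strongest reply is that the rule protects itself. The baseline is a maximum, so a low exacerbation reading does nothing once a higher stable reading lies within 180 days, and 3-monthly collection is designed to supply about two. This stands, and it confines the problem to PERITs with a gap in routine readings. It does not remove the problem. The section on additional consent provisions {26b} says the cohort performs no investigations outside routine care, so a reading each quarter is not guaranteed, and the fallback clause itself anticipates gaps.

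A second reply is that the label already states the right target and that record selection belongs in the analysis plan. That would hold if the article were silent. It instead fixes the window, threshold and fallback test explicitly, and the rule as written departs from its own label.

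A reader might also infer that treatments used more often in rarely seen patients would look better. The documents do not support that. Nothing in them links treatment choice to visit frequency, and where a nested study randomises treatment, visit frequency would not systematically favour one arm.

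**Conclusion.** The defect is real but narrow. When the only reading in the last 180 days is a pre-dose exacerbation reading and a higher stable value lies further back within 365 days, the written rule uses the sick value and overcalls return to at least 90% of baseline. When no other reading exists in 365 days, it yields a result where there is no valid baseline.

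The size cannot be read from the documents. It is near 0% of PERITs with complete 3-monthly spirometry, and at most about 3-12% if 10-30% of routine readings are missed independently.

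Two stronger readings should be resisted. A reader might infer that the recovery outcome in general depends on whether spirometry came before or after the dose; this is not so for anyone with a higher stable reading in the window. A reader might also want a definite inflation of the recovery proportion, but the documents give neither the affected share nor the share misclassified within it. The primary endpoint and the absolute and proportional ppFEV1 changes do not use this baseline and are unaffected. This is a worthwhile correction to one secondary endpoint.

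**What to change.** Amend the baseline definition in Outcomes {12}. Exclude the start-of-therapy reading used for the primary endpoint, and any other reading in a stated interval before the first IV dose (for example 14 days), from both the maximum and the test that opens the 365-day fallback. If no reading then remains in 365 days, set the endpoint to missing.

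Excluding the start-of-therapy reading is the core of the repair. The 14-day figure is borrowed from the limit on how old that reading may be; it does not mark exacerbation onset, so the sponsor should choose and justify the interval.

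The change is about one sentence and needs no new data, because spirometry for the 12 months before enrolment is already collected. There are three costs:

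- Some PERITs become missing. In the model above this is the simulated share with no reading in days 14-180 minus the share with one in days 180-365: 2.60 − 2.58 = 0.02% at 10% missed, 7.00 − 6.73 = 0.27% at 20%, and 12.75 − 11.63 = 1.12% at 30%.
- Some stable readings close to the dose are discarded.
- A sick reading earlier than the interval could still count, since a PERIT may develop subacutely.
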